## Abstract

**Background/Objectives**: Physical exercise (PE) has been shown to have positive effects on the symptoms associated with autism spectrum disorder (ASD). However, there is still no consensus on the most appropriate PE intervention model. With this in mind, we developed a program with the aim of determining the effects of PE on physical fitness, with a view to applying it as a potential treatment. **Methods**: Using an experimental methodology, this research work will recruit 18 institutionalized young people and adults who will be allocated to one of two groups, namely (i) the youth training group and (ii) the adult training group, using low-cost materials. Both intervention groups will perform 90 min of training per session, twice a week, for 12 weeks. Evaluations will be carried out at baseline and month 3. The impact of the exercise program will be assessed based on the variables of anthropometry, body composition, cardiovascular response, and cardiorespiratory fitness. **Results**: The results of this study will contribute to the development of more effective strategies, prescription recommendations, and interventions as a guarantee in future programs of better and greater adherence to PE by institutionalized individuals with ASD. **Conclusions**: In addition, we intend to make the PE program available if it promotes positive effects in the target population.

## 1. Introduction

According to the American Psychiatric Association [1], autism spectrum disorder (ASD) is a complex category of neurobiological developmental disorders, typically diagnosed in childhood. According to the Diagnostic and Statistical Manual of Mental Disorders (DSM-5-TR) [1], this disorder is categorized into three dimensions, namely impairments in verbal and non-verbal communication, impairments in social interaction, and the presence of repetitive and stereotyped behaviors, with an estimated prevalence of around 1% in the global population [2].

Recent evidence suggests that motor behaviors are present in more than 87% of individuals diagnosed with ASD [3], making these individuals functionally dependent on caregivers, resulting in low health-related quality of life (QoL) scores compared to their typically developing peers [4]. This population has lower levels of physical activity (PA) compared to their peers of the same age [5,6,7]. A recent study compared the PA levels of adults with ASD with typically developing adults and found that only 10% of participants with ASD reported completing frequent PA, compared to 50% in the neurotypical group [8].

In addition to being inactive, individuals with ASD are a mostly sedentary population [9], not meeting the recommendations for maintaining or improving their health [10]. The most recent guidelines for adults indicate at least 150–300 min of moderate-intensity PA or 75–150 min of vigorous-intensity PA per week. People with ASD should also participate in exercise sessions that focus on aerobic capacity and muscle strength, involving the main muscle groups, at least 2 days a week [11]. As a result of an inactive and sedentary lifestyle, it is clear that this population has a worsened body composition and a reduced aerobic capacity and muscle strength [12,13,14]. One of the possible reasons for these low levels of PA is the existence of barriers that hinder its practice. Among them, we can find factors such as the financial cost and the lack of adapted exercise programs (EPs), both for individuals and for support institutions [15,16]. In addition, the development of these adapted EPs can contribute to reducing the risk of metabolic and cardiovascular diseases, which reduces health costs and promotes physical fitness, functionality, and QoL.

Given the increasing prevalence of ASD and the lifelong nature of this condition, it has become imperative to address the health and well-being needs of this population throughout all stages of life. The transition to adulthood is a critical period, marked by significant changes that include a downward trend in the practice of physical exercise, which is widely documented in the literature [17,18,19]. In addition, physical exercise has been recognized as an effective non-pharmacological intervention to improve not only the physical condition but also the behavioral, social, and emotional aspects of people with ASD. To date, only three systematic reviews have included participants aged between 18 and 30 [19,20,21], highlighting a lack of data and clear guidelines for prescribing exercise programs that meet the specific needs of this population. Grouping young people and adults allows us to investigate how physical exercise can be an effective intervention to mitigate the challenges associated with this transition, promoting the maintenance of an active lifestyle.

The aim of this study was to evaluate the effects of a 12-week PE program on the anthropometry, body composition, cardiovascular response, and cardiorespiratory fitness of institutionalized young people and adults with ASD. The following hypotheses will be defined: (i) the youth group (YG) will display a significant improvement in all the variables assessed after a 12-week physical exercise program; (ii) the adult group (AG) will display a significant improvement in all the variables assessed after a 12-week physical exercise program; and (iii) one of the groups (YG or AG) will display a significantly greater improvement in all the variables assessed compared to the other group, after a 12-week physical exercise program.

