## 2. Materials and Methods

### 2.1. Design of the Study

This protocol describes a non-randomized experimental study, following the Consolidated Standards of Reporting Trials statement [22], with the aim of evaluating the effectiveness of two combined physical capacities (aerobic capacity and muscular strength). Participants will be allocated to one of two groups: youth training (YT) or adult training (AT).

Participants will take part in a supervised PE program for 12 weeks, twice a week, for 90 min per session. All outcome measures will be collected at two different times, at baseline (time 0, baseline assessment, week 0) and at the end of the intervention (time 1, final assessment, week 12). Figure 1 shows the study design.

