#### 3.1.3. Body Composition

The Inbody 770 (InBody Co., Ltd, Seoul/South Korea), an advanced bioimpedance device that assesses body composition with proven precision, will be used. It is an ideal tool for ongoing research, as it covers an age range of 3 to 99 years, and is also a safe, non-invasive, and fast method. In this sense, it is a technology that uses direct segmental multi-frequency bioimpedance (DSM-BIA) measurement, a tetrapolar system with eight electrodes, which varies the frequency from 1 to 1000 KHz, with an approximate measurement time of 60 s [36].

The following parameters will be obtained from the assessment: total body water; extracellular water; intracellular water; bone mineral content; degree of obesity; body composition history; impedance and reactance of each segment; total and segmental body phase angle; body and segmental edema index; body fat index; fat-free mass index; body cell mass; lean mass of each body segment; estimated segmental fat; skeletal muscle mass; minerals; visceral fat level; body fat percentage; protein; waist-to-hip ratio; and basal metabolic rate.

The participant should climb onto the equipment platform barefoot to establish contact with the four electrodes on their feet. After being prompted by the device, they should take the two electrodes in their hands and move their upper limbs away from their torso, maintaining this position and looking straight ahead.

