#### 3.1.11. Statistical Analysis

Descriptive parameters such as the mean and standard deviation will be used in the statistical analysis. The normality of the data will be checked using the Shapiro–Wilk test. Significant differences between groups will be analyzed using the Kruskal–Wallis test, while differences between assessment times will be investigated using the Wilcoxon test. The choice of non-parametric statistics is based on the central limit theorem, which suggests that in order to obtain a normal distribution, a minimum sample size of 30 participants is required [53]. The magnitudes of the differences will be assessed by Cohen’s d effect size [54]. In addition, associations between study variables will be checked using Spearman’s correlation coefficient [55]. The significance level adopted for all analyses will be *p* < 0.05. The data will be processed using the Statistical Package for the Social Sciences (SPSS) software, version 28, Chicago, IL, USA.

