We intend to contribute with implications for practice with new interventions with physical exercise, prescription, and effective strategies, which we believe can contribute, at all levels, to the well-being of individuals with ASD. If the program proves to be effective, it could be implemented in institutions, schools, or clinics specializing in the prevention and treatment of symptoms in young people and adults with ASD, resulting in a tool to improve health-related QoL, but it will also promote greater inclusion and participation in regular physical activities, contributing to the general well-being of this population.

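### Every hypothesis demands significance on all variables and no outcome is primary, so the plan has no workable rule for deciding whether the program succeeded

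*Protocol article*

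**What the plan says.** The Introduction sets three hypotheses. The first two state that the youth group, and then the adult group, "will display a significant improvement in all the variables assessed" after 12 weeks. The third states that one of the groups, not specified which, "will display a significantly greater improvement in all the variables assessed compared to the other group".

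The Abstract gives four domains equal standing: "The impact of the exercise program will be assessed based on the variables of anthropometry, body composition, cardiovascular response, and cardiorespiratory fitness". Section 2.1 treats the outcomes alike: "All outcome measures will be collected at two different times". No section names a primary outcome.

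Section 3.1.3 lists 21 bioimpedance headings, among them "impedance and reactance of each segment; total and segmental body phase angle; body and segmental edema index", without saying for any of them which direction is an improvement.

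Section 3.1.11 plans Wilcoxon tests over time, Kruskal–Wallis tests between groups and Spearman correlations among study variables. It then states: "The significance level adopted for all analyses will be" p < 0.05. It mentions neither multiplicity nor exploratory status.

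On size, the Abstract says "this research work will recruit 18 institutionalized young people and adults" and gives no split between the groups. On use of the results, the Discussion says: "If the program proves to be effective, it could be implemented in institutions, schools, or clinics". The Abstract likewise makes release of the program depend on beneficial effects, without naming an outcome.

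**The concern.** A success rule should tell the reader in advance which results count as support and which do not. This plan can be read in two mutually exclusive ways, and both go wrong.

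- **Strict reading.** A hypothesis is supported only if every listed variable improves significantly. Some listed items have no defined improvement, and one (the body composition history) is not an outcome. Section 2.6 regards lean mass that is merely held steady as a favorable adaptation, yet under this rule an unchanged lean mass would defeat the hypothesis.
- **Variable-by-variable reading.** Each p-value below 0.05 is reported as a finding in its own right. With this many tests, some are likely to be significant even if nothing changed, and the plan does not say which ones bear on the claim that the program works.

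At stake is whether the trial can give an interpretable answer on effectiveness, the condition that the article attaches to wider use of the program.

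**Working it through.** The article states no power, effect size, SD or family-wise error rate, so there is no figure of its own to reproduce.

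**Inputs from the protocol article:** N = 18; p < 0.05 throughout; Wilcoxon within groups and Kruskal–Wallis between groups; the variable lists in sections 3.1.2 to 3.1.6.

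**Assumptions:** a 9/9 split; two-sided tests; normally distributed changes; correlations between variables from 0 to 0.8. The variable count is 3 anthropometric (body mass, BMI, waist) + 20 bioimpedance (21 headings less the history item, each segmental family counted once) + 3 resting cardiovascular + 2 fitness = 28.

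**1. Strict reading.** If each variable had 80% power and all were independent, the chance that all 28 succeed is 0.8^28 = 0.2%. To reach 80% jointly, each would need 0.8^(1/28) = 99.2% power. Simulating the exact two-sided signed-rank test in one group of 9, with the same true change on every variable and a common correlation, gives these chances that all 28 are significant:

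| True change (SD of change) | Power per variable | Corr. 0 | Corr. 0.5 | Corr. 0.8 |
|---|---|---|---|---|
| 0.8 | 49% | 0% | 1.5% | 11% |
| 1.0 | 68% | <0.1% | 6.9% | 25% |
| 1.5 | 95% | 27% | 57% | 76% |

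For hypothesis (iii), with 9 against 9 and a true difference of 1.0 SD on all 28 variables, the chance is 0%, 2.3% and 12.5% at correlations 0, 0.5 and 0.8.

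**2. Small groups.** The smallest exact two-sided signed-rank p is 2/2^n. At n = 5 it is 2/32 = 0.0625, so a group of 5 or fewer cannot reach 0.05. The plan does not say whether p-values will be exact. The uncorrected normal approximation at n = 5 gives z = 7.5/√13.75 = 2.02, p = 0.043, so this limit belongs to the exact test.

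**3. Variable-by-variable reading, nothing truly changing.** There are 28 × 3 = 84 tests. The exact signed-rank test at n = 9 has size 0.0391, so about 56 × 0.0391 + 28 × 0.05 = 3.6 significant results are expected. Simulated chance of at least one across the three hypotheses:

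- 28 variables, independent: 95%
- 28 variables, within-domain correlation 0.3, 0.5, 0.8: 92%, 87%, 72%
- 28 variables, correlation 0.8 across all: 51%
- only the 8 non-bioimpedance variables: 58% (independent) to 33% (0.8 across all)

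These figures count significant worsening too. A false improvement in one group of 9 has chance 0.0391/2 = 0.0195 per variable, which over 28 independent variables gives 1 − 0.9805^28 = 42%. It is about 24% at correlation 0.5 and 13% at 0.8. Spearman tests come on top.

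**4. Adjusting the whole list is not a way out.** Bonferroni over 28 variables is 0.05/28 = 0.0018, below the smallest attainable exact p at n = 9, which is 2/512 = 0.0039. No within-group test could pass.

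**The case against.** Several points on the other side have force.

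- **The two harms do not occur together.** Under the strict rule all tests must succeed, and that does not inflate type I error. Inflation arises only if single p-values are read as evidence. This stands: the defect is that the text does not choose between the readings.
- **The chance of a false finding can be overstated.** Treating the 84 tests as independent gives 1 − 0.95^84 = 98.7%, and a reader might infer that chance findings are almost certain. The documents do not support that. Hypothesis (iii) reuses the data of (i) and (ii), and many bioimpedance outputs come from one measurement and overlap.
- **The count of 28 is one reading.** Section 3.1.3 says what the device will yield, not that each output will be tested. The hypotheses, however, speak of everything assessed.
- **Roll-out.** A reader might infer that any single p < 0.05 would trigger it. Section 3.1.11 sets no such rule, and the Discussion is conditional. What stands is that no deciding outcome is named.
- **Pooling.** A reader might infer that the 18 should be analyzed together because the aim concerns one program. Section 2.2 gives developmental reasons for separating ages 10–17 from 18–65, and pooling presumes a common effect. The analysis text does not exclude it either. It is an option, not a correction.
- **Pilot status and details left elsewhere.** The Discussion calls the study a pilot, but also expects the results to confirm the hypothesis. Multiplicity detail may sit in a document not shown. The all-variables wording and the blanket 0.05, though, are stated here, and a later document could only contradict them.

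**Conclusion.** The concern holds: the hypotheses as worded, with no primary outcome and a uniform 0.05, give no interpretable yes or no.

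On the strict reading, success in one group is very unlikely for true changes up to about 1 SD on every variable (at most about 11% at 0.8 SD and 25% at 1.0 SD). It is not out of reach if every variable changes by 1.5 SD (27–76%). On the other reading, at least one chance significant result is likely, at about 50–95% with 28 variables, but not certain.

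All these figures rest on the assumed 9/9 split, the variable count, the correlations and equal effects on all variables, none of which the article gives. The defect in the rule itself rests on none of them.

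**What to change.** Before data are seen:

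1. Replace the all-variables wording in hypotheses (i)–(iii) with one named primary outcome that has a stated direction of benefit and is measured in both groups. Six-minute walk distance is one example; the choice is the investigators'.
2. Test it once per hypothesis: exact Wilcoxon signed-rank for (i) and (ii), and the planned between-group test on the change for (iii). With 9 per group, 80% power needs a change of about 1.15 SD within a group and a difference of about 1.45 SD between groups.
3. Optionally add a pooled test in all 18, which needs about 0.75 SD, with the common-effect assumption stated.
4. Name at most one key outcome for each of the three remaining domains, with Holm adjustment. The strictest step is 0.05/3 = 0.0167, which is attainable at n = 9 (smallest p 0.0039) but not in a group of 6 or fewer (2/64 = 0.031).
5. Report the other bioimpedance outputs and all Spearman correlations as exploratory estimates with 95% confidence intervals and no significance claim.

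The cost is a change of wording, fewer significance claims, and the notification to the ethics committee that section 2.4 requires before a protocol change is implemented. It does not cure the lack of a control group, so even a clear primary result would show change over time and could not by itself be credited to the program.

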## 2. Materials and Methods

### 2.1. Design of the Study

This protocol describes a non-randomized experimental study, following the Consolidated Standards of Reporting Trials statement [22], with the aim of evaluating the effectiveness of two combined physical capacities (aerobic capacity and muscular strength). Participants will be allocated to one of two groups: youth training (YT) or adult training (AT).

Participants will take part in a supervised PE program for 12 weeks, twice a week, for 90 min per session. All outcome measures will be collected at two different times, at baseline (time 0, baseline assessment, week 0) and at the end of the intervention (time 1, final assessment, week 12). Figure 1 shows the study design.

### 2.2. Participants

The program will involve volunteers, comprising young people and adults who are institutionalized in a care facility located in Coimbra (Portugal), recruited using the non-probabilistic convenience method. The YG will include individuals aged 10–17, and the AG will include individuals aged 18–65. This division is based on criteria widely recognized in the literature. Adolescence (10–17 years) is a critical phase of development characterized by rapid physiological and cognitive changes [23]. The adult age group (18–65 years), on the other hand, covers a wide range of stages, from early adulthood to middle age [24]. In the first stage, there will be an individual explanation of the objectives and procedures of the study, as well as the potential benefits, risks, and time required for its development. Secondly, participants/family members/legal guardians will sign an informed consent form.

The inclusion criteria will be as follows: (i) having a certified medical diagnosis of ASD (autistic disorder, Asperger’s syndrome, or pervasive developmental disorder without other specification) according to the standards established in the DSM-5-TR [1]; (ii) ages between 10 and 65 years; (iii) a recent history of non-participation in PE programs or similar physical motor activities; (iv) success in performing movements such as running, pulling, and pushing; (v) ability to perform the assessments; and (vi) attendance at least 75% of the total 24 sessions. The exclusion criteria will be defined as follows: (i) individuals who are unable to commit for 3 months; (ii) individuals with other associated pathologies; (iii) clinical contraindications; (iv) inability to walk without support; (v) inability to communicate; (vi) failure to provide signed informed consent; and (vii) individuals over the age of 18 who do not agree to take part in the study. Specific data on socio-economic status and level of education will not be recorded.

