### 2.5. Intervention Assignment and Blindness

Once the initial assessments have been completed, the volunteers will be allocated to the two groups according to their age group. Due to the nature of the intervention, it will not be possible to randomize the sample into groups nor to “blind” participants and the principal investigator.

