## 4. Discussion

This pilot study aims to evaluate the effects of a 12-week physical exercise program on anthropometric variables, body composition, cardiovascular response, and cardiorespiratory fitness in young people and adults with ASD. The results are expected to confirm the hypothesis that physical exercise provides significant physiological benefits based on adaptations in the cardiovascular and musculoskeletal systems, contributing to an overall increase in exercise capacity. These results should reinforce the use of exercise as an effective tool in the prevention and treatment of cardiometabolic diseases, the promotion of physical fitness, the improvement of performance in activities of daily living, and the reduction in restrictive and repetitive behaviors often observed in individuals with ASD.

The pilot study that will follow is essential to understand whether this exercise program is effective in reducing the barriers that hinder the practice of physical exercise by young people and adults with ASD, taking into account the low levels of physical fitness of this population [5,6,7], revealing a strong multidisciplinary approach, since it is prudent to evaluate the combined effects of exercise with independent variables. The exercise program will be supported by a quarterly plan, which includes the number of sessions, the didactic function of each session, the distribution of content per session, and the list of materials.

As with all studies, ours has some limitations, among which we highlight the following: (i) due to logistical constraints, it will not be possible to randomize the groups; (ii) due to limitations in recruiting participants, it will not be possible to implement a control group and (iii) it will not be possible to control the physical activities carried out outside the exercise program, which could positively or negatively influence the variables studied.

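### With no control group and no growth-adjusted outcome, normal growth in the 10–17-year-olds can mimic or hide a programme effect in individual variables and confounds the youth-versus-adult comparison

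*Protocol article*

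**What the plan says.** - **Groups.** Section 2.2: "The YG will include individuals aged 10–17, and the AG will include individuals aged 18–65". Section 2.5: "the volunteers will be allocated to the two groups according to their age group". Both groups receive the programme.
- **The youth band.** Section 2.2 justifies the split partly because "Adolescence (10–17 years) is a critical phase of development characterized by rapid physiological and cognitive changes".
- **Timing.** Section 2.1 measures all outcomes twice, "at baseline (time 0, baseline assessment, week 0) and at the end of the intervention (time 1, final assessment, week 12"). There is no run-in or second baseline.
- **Outcomes.** Section 3.1.2 takes height, mass, waist and plain BMI. Section 3.1.3 lists absolute body-composition outputs such as total body water, bone mineral content, skeletal muscle mass and basal metabolic rate. It also lists some outputs that are already indexed: "body fat index; fat-free mass index; body cell mass; lean mass of each body segment" names two indices beside two absolute masses.
- **Tests.** Section 3.1.11 uses Wilcoxon between times and Kruskal–Wallis between groups, at p < 0.05. It states no age standardisation or allowance for maturation.
- **Hypotheses.** Section 1: (i) youths improve significantly on every assessed variable; (ii) adults do the same; (iii) one group improves more than the other on every assessed variable.
- **Interpretation.** Section 4 concedes that "due to limitations in recruiting participants, it will not be possible to implement a control group". It also says in advance: "These results should reinforce the use of exercise as an effective tool in the prevention and treatment of cardiometabolic diseases". Growth is not among the three limitations listed.

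**The concern.** A before-after change in an untreated adolescent is not expected to be zero for quantities that scale with body size. With no concurrent control and no second baseline, the youth change is programme effect plus growth, and nothing in the design separates the two. The protocol names the source of the problem in section 2.2, then defines its two groups so that this source sits wholly in one of them.

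Two readings are at stake. Within youths, a significant rise in lean or muscle mass would be credited to training. Between groups, a youth-adult difference would be read as one age group responding better, when part or all of it could be growth. The error can also run the other way: mass, BMI and waist tend to rise with growth, so a real benefit in these could be cancelled. The article contemplates use in institutions, schools or clinics if the programme proves effective, so the attribution matters.

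**Working it through.** The protocol gives no effect size, SD of change or power for its sample size, so there is no figure of its own to reproduce. The check asks how often the planned tests would be significant when the programme has no effect.

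**Inputs from the document:** total of 18 (Abstract); ages 10–17 and 18–65 (2.2); 12 weeks (2.1); Wilcoxon, Kruskal–Wallis and p < 0.05 (3.1.11).

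**Assumptions:** two-sided tests; 6, 9 or 12 youths out of 18, since no split is given; fat-free mass gain in youths of 2–4 kg/year and none in adults; SD of the 12-week change 0.6–0.7 kg; normally distributed changes; Kruskal–Wallis applied to the changes.

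**Step 1: growth over 12 weeks.** Gain = yearly rate × 12/52.
- 2 × 12/52 = 0.46 kg
- 4 × 12/52 = 0.92 kg

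**Step 2: standardised drift.** Drift = gain / SD.
- Smallest: 0.46/0.7 = 0.66
- Largest: 0.92/0.6 = 1.54

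**Step 3: probability of a favourable significant Wilcoxon result in youths, zero programme effect** (simulated, exact test).

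| Gain per year, SD | Drift | 6 youths | 9 youths |
|---|---|---|---|
| 2 kg, 0.7 kg | 0.66 | 17% | 35% |
| 2 kg, 0.6 kg | 0.77 | 22% | 46% |
| 4 kg, 0.7 kg | 1.32 | 55% | 90% |
| 4 kg, 0.6 kg | 1.54 | 68% | 96% |

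Without drift the corresponding figure is about 2%. At smaller drifts, plausible for youths near the end of growth, it falls quickly: with 9 youths, 8% at 0.25 SD and 22% at 0.5 SD.

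**Step 4: Kruskal–Wallis, youths against adults, same assumptions, 9 per group.** False significance is 25% at a drift of 0.66 and 85% at 1.54, against about 5% with no drift. With a 6/12 split the figures are 23% and 81%.

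**Step 5: hypothesis (i) as worded, requiring every variable** (9 youths, correlation between variables 0 to 0.8).
- All 10 variables drift favourably by 1 SD: 2% to 35%.
- Half of them have no drift: at most 0.2% with 10 variables, at most 0.8% with 4.
- Half drift unfavourably by 0.5 SD: about 0.
- In the two mixed settings, at least one of the 10 variables shows a false improvement in about 88% to nearly 100% of trials.

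**The case against.** **Growth confirming hypothesis (i) outright.** A reader might infer that growth alone could do this. The wording does not support it. The hypothesis covers every variable, which takes in blood pressure, resting heart rate, the walk and step tests and body fat percentage. Growth cannot be expected to improve all of them, and step 5 shows how small the chance is. Hypothesis (iii) carries the same requirement, so growth confounds its individual comparisons but is unlikely to decide it whole.

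**A bias that always flatters the programme.** A reader might also infer this. It favours the programme for lean and muscle mass and works against it for mass, BMI and waist, where a rise would not normally count as improvement. Height is a poor example of a false effect: it is measured and feeds BMI, and nowhere is a gain in height called an improvement.

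**Disclosure and condensation.** The article states that there is no control group and no randomisation, and calls the study a pilot. Section 3.1.3 lists device outputs without saying that each will be tested, and some are already indexed. An analysis plan that is not shown might add age-standardised scores. These points have weight. But the hypotheses, tests and interpretation are stated in the article, the limitations do not mention growth, and disclosing the missing control leaves the effectiveness reading as it was.

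**Size.** The percentages depend on assumed growth rates, SDs and group split, and with little remaining growth the problem is small. That is correct, and it is why ranges are shown.

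**Conclusion.** The concern holds variable by variable and for the youth-adult contrast. As the plan stands, normal growth can make absolute lean mass, skeletal muscle mass, bone mineral, body water or basal metabolic rate significant in youths with no programme effect. It can hide benefit in mass, BMI and waist, and it is inseparable from group in hypothesis (iii).

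For fat-free mass the false favourable rate is about 35–96% with 9 youths and 17–68% with 6. These figures rest entirely on the assumed gain, SD and split. The confounding itself does not depend on them: it follows from the age-defined groups, the two measurements and the absence of a control. The documents do not support the claim that growth alone would confirm hypothesis (i) as worded.

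**What to change.** 1. For youths, test size-indexed outcomes already available from the planned measurements: fat-free mass index, body fat index, body fat percentage and waist-to-height ratio. Use BMI-for-age z-score for the within-youth test only, because it has no counterpart on the same scale in adults.
2. Report youth height, mass and absolute lean, water, bone and basal metabolic rate values descriptively.
3. Limit hypothesis (iii) to measures defined on the same scale in both groups, and leave out absolute growth-dependent values.
4. Add growth and maturation to the limitations in section 4.
5. Word the aim, hypotheses and conclusions as change over 12 weeks, not as programme effect or effectiveness. This is needed even after steps 1 to 3, because indexing reduces the bias without removing it and does nothing for blood pressure, walk-test or step-test results.

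The cost is confined to analysis and wording; no new measurement is required. The sponsor must choose a growth reference, will have fewer variables in hypothesis (iii), and will make a more modest claim.
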